#### Sample size

2.2.4

The sample size was determined using the following formula for comparing means between two groups from Medical Statistics (edited by Sun Zhenqiu) (30):
n=2[(Zα/2+Zβ)δσ]2

Based on previous published findings (31), sham acupuncture resulted in a post-treatment PSQI score reduction to 11.69 ± 3.35 (mean±SD), with a sample standard deviation (s) of 3.35. We hypothesized that acupuncture would yield an additional 2.70-point reduction in PSQI scores compared with that associated with sham acupuncture. The statistical hypothesis test of the evaluation variable is two-sided, and the significance level is set at 5%. The type 2 error (*β*) will be set to 0.1. The calculation yielded n = 31.52 ≈ 32 per group. Accounting for a 20% dropout rate based on clinical experience, the final required sample size was 38 participants per group (76 total participants).

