### Participants and setting

2.2

We will recruit eligible participants who meet the operational definition of glucocorticoid-induced insomnia described below from the Acupuncture Department of the First Affiliated Hospital of Zhejiang Chinese Medical University. Subjects will be randomly assigned to 2 parallel groups based on randomization numbers: the acupuncture group and the sham acupuncture group, with an enrolment ratio of 1:1. Written informed consent will be obtained from all participants. This study was approved by the ethics committee of the First Affiliated Hospital of Zhejiang Chinese Medical University (no. 2024-KLS-089-02). This study will be conducted in accordance with the Declaration of Helsinki.

Operational definition of glucocorticoid-induced insomnia: In this trial, GII is operationally defined as insomnia meeting the applicable ICSD-3 diagnostic criteria (26) after documented systemic glucocorticoid exposure. Eligible patients must have either new-onset insomnia or a clear worsening of pre-existing mild sleep complaints that did not meet full ICSD-3 criteria before the index exposure, with full diagnostic criteria first met within 14 days after glucocorticoid initiation or clinically meaningful dose escalation, while receiving glucocorticoids at ≥5 mg/day prednisone equivalent. Patients who met full ICSD-3 criteria for insomnia before the index glucocorticoid exposure will not be eligible. The diagnosis will be based on a structured clinical interview, medical record review, a 1-week sleep diary, PSQI >5, ISI assessment, and baseline polysomnography showing objective total sleep time <6 h, consistent with recommended insomnia assessment procedures (27).

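### The sample-size calculation does not support 90% power with 20% dropout: 38 per group leaves about 30 evaluable, fewer than the 32 the same paragraph requires

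*Protocol article*

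**What the plan says.** The calculation is in section 2.2.4 (Sample size) of the protocol article. It is for a two-group comparison of means ("The sample size was determined using the following formula for comparing means between two groups") and takes the spread from a published sham arm, "with a sample standard deviation (s) of 3.35". The target is "We hypothesized that acupuncture would yield an additional 2.70-point reduction in PSQI scores" relative to sham. The test is two-sided at 5%, and the type 2 error "will be set to 0.1", so the intended power is 90%. Allocation is 1:1 (section 2.2).

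The stated result is "The calculation yielded n = 31.52 ≈ 32 per group". After an allowance for 20% dropout, "the final required sample size was 38 participants per group (76 total participants"). The paragraph does not show how the allowance was applied. It mentions no t-correction and no gain from baseline adjustment.

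**The concern.** All inputs and both results are printed, so the paragraph can be checked on its own terms. Two things stand out. The first-step figure of 31.52 is not what the formula appears to give. And 38 per group looks too small to leave 32 after a fifth are lost.

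This paragraph is the only justification the article gives for 76 patients. If it is wrong, readers are told that the trial has 90% power with 20% loss when its own calculation does not show that.

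**Working it through.** **Inputs** (section 2.2.4; allocation from section 2.2): SD σ = 3.35; difference δ = 2.70; two-sided α = 0.05, z = 1.960; β = 0.1, z = 1.2816; 1:1 allocation; dropout 20%. The formula's fraction is flattened in the text available here. It is read in its standard form, n per group = 2[(z_α/2 + z_β)·σ/δ]².

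**Step 1: the base n.**

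- n = 2 × [(1.960 + 1.2816) × 3.35/2.70]² = 32.35, so 33 per group.
- With z rounded to 1.96 + 1.28, n = 32.32, still 33.
- A one-sided 5% test gives 26.4. A two-sample t-test needs 34.
- Rounding of the inputs does not explain the gap: SD 3.345 with difference 2.705 still gives 32.14.
- To obtain 31.52, the difference would have to be about 2.735 (with SD 3.35) or the SD about 3.307 (with difference 2.70).

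The printed 31.52 is therefore not reproduced. The gap is 32.35 − 31.52 = 0.83, or one patient per group after rounding up.

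**Step 2: the dropout allowance.** To keep n evaluable after a loss d, randomise n/(1 − d).

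- From the protocol's own 32: 32/0.8 = 40 per group, 80 in total.
- From the recomputed 33: 33/0.8 = 41.25, so 42 per group, 84 in total.
- Multiplying instead: 31.52 × 1.2 = 37.8, which rounds up to 38.

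The stated 38 fits the multiplication and not the division. In the other direction, 38 × 0.8 = 30.4, below the 32 that the same paragraph requires.

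**Step 3: power for a difference of 2.70 with SD 3.35.**

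| Evaluable per group | Normal formula | Two-sample t-test |
|---|---|---|
| 30 | 87.7% | 86.6% |
| 30.4 (38 less 20%) | 88.1% | 87.1% |
| 32 | 89.7% | 88.8% |
| 33 | 90.6% | 89.7% |
| 34 | 91.4% | 90.6% |
| 38 (no loss) | 94.0% | 93.4% |

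**Step 4: detectable difference at 90% power, normal formula.** δ = (1.960 + 1.2816) × 3.35 × √(2/n).

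- n = 30.4: 10.859 × 0.2565 = 2.79.
- n = 30: 10.859 × 0.2582 = 2.80.

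**Step 5: loss that 38 per group can absorb.**

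- For 33 evaluable: 1 − 33/38 = 13.2%.
- For the protocol's 32: 1 − 32/38 = 15.8%.

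Both are below the 20% allowed for.

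**The case against.** The best defence is that the calculation does not describe the planned analysis. Section 2.6.2 specifies a mixed model for repeated measures adjusted for baseline PSQI, using all available post-baseline data, with the primary contrast at the post-treatment visit. Baseline adjustment normally reduces residual variance. Withdrawal under section 2.2.3 includes loss during follow-up, and a participant lost only then may already have given the post-treatment PSQI. Section 2.6.1 keeps participants who take unauthorised sedative-hypnotics in the full analysis set. So 30 evaluable per group at the primary visit is the pessimistic end. If all 38 contributed, power would be 93% to 94% even without adjustment.

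This stands as a limit on the claim. A reader might infer that the trial itself has only 87% or 88% power. The document does not support that, because it gives neither a baseline-to-post correlation nor a split of dropout by phase. But section 2.2.4 uses neither argument. It applies an unadjusted two-means formula and presents 38 as the number that covers 20% dropout. An assumption that is not stated cannot repair the calculation that is.

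A reader might also take 38 to be 32 × 1.2 = 38.4 wrongly rounded down, which would add a further error. The document does not show that. No inflation formula is printed, and 31.52 × 1.2 = 37.8 rounded up gives 38 just as well.

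**Conclusion.** The concern holds for the stated calculation. The main error is the dropout step: 38 per group does not leave the required number after 20% loss, whether that number is the protocol's 32 (needs 40) or the recomputed 33 (needs 42). The base n is a smaller slip, 32.35 against the printed 31.52.

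On the protocol's own normal formula, power at 20% loss is about 88%, and about 87% by t-test, so the type 2 error is about 0.12 to 0.13 and not 0.10. These figures rest on the stated SD and difference, an unadjusted comparison, and the whole 20% being missing at the post-treatment visit.

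The shortfall is 2 to 3 percentage points of power. It affects neither bias nor the type 1 error, and it does not make the design unsound. It is a text correction of moderate severity.

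**What to change.** Keep 76 patients and restate the paragraph in section 2.2.4 with one method throughout. For example:

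> The formula gives 32.35, i.e. 33 evaluable participants per group. With 38 randomised per group and 20% loss (about 30 evaluable), power for a 2.70-point difference is about 88% by this formula (about 87% by t-test). By this formula, 90% power is kept only if loss is at most about 13%.

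The normal formula and the t-test should not be mixed without labels: 33 per group meets 90% by the normal formula but gives 89.7% by t-test.

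If the sponsor wishes to claim more power from the baseline-adjusted model, it should state the assumed baseline-to-post PSQI correlation and an independent source for it. Recruitment has been under way since February 2025 (section 4), so a correlation solved backwards to restore 90% would be an after-the-fact justification.

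The cost is one paragraph of text and a slightly less favourable power statement. No extra patients are needed.

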#### Randomization

2.2.5

An independent statistician generated a 1:1 allocation sequence in SPSS 25.0 (IBM Corp.) using permuted blocks of undisclosed varying sizes. The master allocation list and random seed are retained by the statistician in a restricted-access file until database lock.

#### Blinding

2.2.6

The allocation sequence is implemented using sequentially numbered, opaque, sealed envelopes prepared by personnel not involved in participant enrolment. Each envelope contains the treatment card corresponding to the next allocation in the sequence. After eligibility is confirmed and written informed consent is obtained, the treating acupuncturist opens the next envelope in numerical order immediately before the first treatment. Envelope integrity and the date and time of opening are documented.

Emergency envelopes labeled with “Emergency Unblinding Document: Clinical Trial of Acupuncture for GII,” containing group assignments (e.g., “Participant ID XXX: [Group]”), were prepared identically to treatment envelopes. Unblinding was permitted only for (1) serious adverse events or (2) life-threatening emergencies requiring immediate intervention, following approval by the principal investigator. Participants with unplanned unblinding will be excluded from the PPS but retained in the FAS and safety analyses.

The database will be locked after blind review and resolution of all data queries. Group allocation will be revealed to the principal investigator and statistician only for the final analysis. Blinding will be considered compromised if full allocation disclosure occurs or if >20% of emergency envelopes are opened during the trial.

This is a single-blind trial with participants blinded to treatment allocation. The acupuncturists are not blinded due to the nature of the intervention. However, all outcome assessors (including those administering the PSQI, ISI, and other questionnaires), PSG scorers, actigraphy analysts, laboratory personnel performing the 5-HT assays, and statisticians are blinded to group assignment until database lock. To assess participant blinding success, a standardized questionnaire will be administered upon completion of the intervention, asking participants to guess their allocated group and rate their confidence. Bang’s Blinding Index will be calculated to quantify the adequacy of blinding. Emergency unblinding is permitted only under predefined conditions (SAEs or life-threatening emergencies) and requires principal investigator approval. Participants with unplanned unblinding will be retained in the FAS and safety analyses but excluded from the PPS as a major protocol violation.

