### Study design

2.1

This study is designed as a single-centre, sham-controlled, randomized controlled trial. This clinical trial will be conducted at the Acupuncture Department of the First Affiliated Hospital of Zhejiang Chinese Medical University. This trial was rigorously designed according to the Consolidated Standards of Reporting Trials (CONSORT) guidelines and the Standards for Reporting Interventions in Clinical Trials of Acupuncture (STRICTA) (Table 1). In addition, the study protocol strictly adheres to the Standard Protocol Items: Recommendations for Interventional Trials (SPIRIT) guidelines (See the supplementary material). The study flowchart and procedure are depicted in Figure 1 and Table 2.

**Table 1 tab1:** STRICTA of acupuncture treatment.

Item	Detail	Description
1. Acupuncture rationale	(1a) Style of acupuncture	Traditional Chinese Medicine
	(1b) Reasoning for treatment provided, based on historical context, literature sources, and/or consensus methods, with reference where appropriate	Textbook of the meridian, literature review of acupuncture for insomnia
	(1c) Extent to which treatment was varied	Formularized
2. Details of needling	(2a) Number of needle insertions per subject per session	4
	(2b) Names	HT7, KI7
	(2c) Depth of insertion, based on a specified unit of measurement, or on a particular tissue level	HT7: Vertical insertion, 0.3–0.5 cun; KI7: Vertical insertion, 0.5–1.0 cun
	(2d) Response sought	de qi
	(2e) Needle stimulation	manual
	(2f) Needle retention time	20 min
	(2g) Needle type	0.25 × 40 mm needles (Andi, Guizhou, China), stainless steel
3. Treatment regimen	(3a) Number of treatment sessions	10
	(3b) Frequency and duration of treatment sessions	Three sessions per week for the first 3 weeks and one session in the final (fourth) week, giving a total of 10 sessions.
4. Other components of treatment	(4a) Details of other interventions administered to the acupuncture group	none
	(4b) Setting and context of treatment, including instructions to practitioners, and information and explanations to patients	All interventions will be administered at a same clinical site by two licensed acupuncturists who will receive identical standardized training in the study protocol prior to trial initiation.

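### Allocation concealment is at risk: the unblinded treating acupuncturist opens the next envelope at the first session, and the article describes no step that binds a participant to an envelope before it is opened

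*Protocol article*

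**What the plan says.** Section 2.2.5 (Randomization) has an independent statistician generate a 1:1 sequence "using permuted blocks of undisclosed varying sizes". On custody it states: "The master allocation list and random seed are retained by the statistician in a restricted-access file until database lock". No strata are named.

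Section 2.2.6 (Blinding) describes "sequentially numbered, opaque, sealed envelopes prepared by personnel not involved in participant enrolment". On timing: "After eligibility is confirmed and written informed consent is obtained", "the treating acupuncturist opens the next envelope in numerical order immediately before the first treatment". On the audit trail: "Envelope integrity and the date and time of opening are documented". On the person who opens: "The acupuncturists are not blinded due to the nature of the intervention".

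Table 1 in section 2.1 (item 4b) adds: "All interventions will be administered at a same clinical site by two licensed acupuncturists". Section 2.7 places the baseline assessment one week before the first session.

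Two other places touch on the link between participant and allocation. Section 2.2 says that assignment is based on randomization numbers. Section 2.2.6 says that emergency envelopes pair a participant ID with a group. Neither says when the number or ID is issued.

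**The concern.** The person who opens the envelope delivers the treatment, learns each allocation they open, and does so at the first session. Eligibility and consent come earlier, so the procedure protects against selective enrolment. It does not, as described, protect against selective ordering of people already enrolled. If two participants are due to start close together, whoever starts first takes the next number. A person who suspects what the next card holds could favour one order over the other without breaking any written rule, and the log would still show intact envelopes opened in sequence.

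Allocation could then depend on expected response, which concealment exists to prevent. The primary outcome is a questionnaire score completed by the participant. The primary model in section 2.6.2 adjusts only for baseline PSQI. Glucocorticoid dose and timing, pain and disease activity are recorded as possible influences on sleep (sections 2.2 and 2.7) but are not in that model, so selection on them would not be removed.

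**Working it through.** The plan gives no figure for this point. The check covers how predictable the next card is, how often two starts fall close together, and what a swap would do to the contrast.

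**1. Predictability.** Block sizes are undisclosed, so those used here are assumptions. The guess is always the arm under-represented so far, with a coin toss when the arms are level.

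- By hand, for blocks of 4 with all earlier cards known, the chance of a correct guess at positions 1 to 4 is 1/2, 2/3, (1/3 × 1 + 2/3 × 1/2) = 2/3, and 1. The mean is (0.500 + 0.667 + 0.667 + 1)/4 = 0.708.
- By simulation of 76 allocations (5,000 runs per scheme; for the last column each participant goes to either acupuncturist at random):

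| Assumed block sizes | All earlier cards known | Own cases only |
|---|---|---|
| 4 | 0.708 | 0.538 |
| 6 | 0.680 | 0.538 |
| 2, 4 | 0.721 | 0.539 |
| 4, 6 | 0.691 | 0.537 |
| 2, 4, 6 | 0.701 | 0.539 |
| 4, 6, 8 | 0.679 | 0.538 |

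The simulated 0.708 for blocks of 4 agrees with the hand calculation. Mixing block sizes leaves the chance above one half. What matters far more is whether one person knows all earlier cards or only their own.

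**2. Opportunity.** Section 4 gives a recruitment start of 20 February 2025 and completion by 20 December 2026: 668 days, or 95.4 weeks. Allowing the 8–9 weeks that section 2.2 gives each participant leaves about 87 weeks. 76/87 = 0.87 starts per week. Assuming even Poisson arrivals:

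- weeks with two or more starts: 1 − e^(−0.87) × (1 + 0.87) = 0.22;
- participants who share a start week with another: 1 − e^(−0.87) = 0.58.

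Sharing a week is not sharing a day, so these figures show that close starts are plausible, not that reordering is easy.

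**3. Size, as illustration.** With 38 per arm (section 2.2.4), swapping one pair whose expected outcomes differ by d points moves each arm mean by d/38 in opposite directions. For k swaps, all favouring the same arm, the shift is 2kd/38.

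| Swaps k | d = 1 | d = 3 |
|---|---|---|
| 0 | 0 | 0 |
| 1 | 2/38 = 0.05 | 6/38 = 0.16 |
| 2 | 4/38 = 0.11 | 12/38 = 0.32 |

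The largest entry is 0.32/2.70 = 12% of the planned effect. The unadjusted standard error is 3.35 × √(2/38) = 0.77, so 0.32 is about 0.4 of a standard error. Adjustment for baseline PSQI would remove any part of d that baseline explains. Both k and d are assumptions.

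**The case against.** A reader might infer three stronger things, and the documents support none of them.

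- **That the acupuncturists know every earlier allocation.** The article names two of them, and each is certain to know only their own cases. Sharing one numbered series at one site makes wider knowledge plausible, but it is not stated, and with own cases only the guess is right about 54% of the time.
- **That nothing links a participant to an envelope in advance.** This is a condensed article, and its silence does not prove absence. Section 2.2 mentions randomization numbers, and the emergency envelopes carry a participant ID. If that ID is issued at enrolment and already tied to a group, it sits badly with allocation by order of first session. If it is issued at opening, it binds nothing beforehand. The text does not say which.
- **That the acupuncturists control the order of starts.** No section says who schedules first sessions.

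The safeguards also deserve their weight: independent generation, a restricted list, undisclosed varying blocks, preparation by people outside enrolment, and logged opening. Opening a card and then choosing its recipient would depart from the written procedure. Starts average below one a week, so there will often be nobody to swap with, and a long delay would show against the one-week interval from baseline.

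All of this limits the risk. It does not answer the central point, because the order of starts can be altered before opening, on a guess, without any departure from the text. Binding the number well before session 1 would carry a cost, since section 2.6.1 leaves anyone untreated outside the full analysis set. That is a reason to bind it late, not to leave it unbound.

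**Conclusion.** The point stands as a correctable risk to allocation concealment. The article states positively that an unblinded treating clinician opens the envelope at the first session, so allocation follows the order of first sessions, and the safeguards it lists do not include fixing the participant to the envelope before opening. Varying blocks reduce prediction without removing it.

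There is no evidence that allocation has been influenced, and none is alleged. The bias could be nil. The 0.32-point figure rests on two assumed swaps, an assumed 3-point difference and the assumption that both swaps favour the same arm. The predictability figures rest on assumed block sizes. The sample size is unaffected and the trial is not invalidated. A change is worth making because recruitment was still open when the article was written and the step costs almost nothing.

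**What to change.** In section 2.2.6, for participants still to be randomised:

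- A staff member already on the trial who does not treat takes the next envelope in order and, while it is sealed, writes the participant ID, date and time on it. This happens at or shortly before arrival for the first session.
- Where several participants are waiting, envelopes are assigned in the order in which baseline was completed.
- Only then does the acupuncturist receive and open the envelope.

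State when the participant ID on the emergency envelopes is issued, and make that consistent with this sequence.

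For those already randomised, compare the order of opening with the order of baseline completion from the recorded dates. This needs no allocations. A mismatch can have innocent causes, so it should prompt a look at the reason and not a conclusion.

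The cost is a small handling step and a dated change of procedure during recruitment, with no extra visits. A participant who is numbered but leaves before session 1 uses up an envelope and should be reported as randomised, though outside the full analysis set. Because the envelope is still sealed at that point, the loss cannot depend on the allocation.

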### Intervention

2.3

The acupuncturists for this study received a master’s degree in acupuncture and tuina at Zhejiang Chinese Medical University, have 8 years of training experience, obtained a doctor qualification certificate and have 3 years of clinical work experience. Participants in both the acupuncture and sham control groups will receive interventions three sessions per week for the first 3 weeks and one session in the final (fourth) week, for a total of 10 sessions.

#### Acupuncture group

2.3.1

The subjects in the acupuncture group will be placed in the supine position. We selected two acupoints for this study: HT7 and KI7. The reason for choosing these acupoints is based on our previous clinical study, which was based on the theoretical framework of TCM according to the Heart-Kidney interaction theory (16). Participants will assume the supine position after the skin is disinfected with 75% alcohol. A disposable sterile stainless steel acupuncture needle with a length of 40 mm and a diameter of 0.25 mm will be used (Andy, Guizhou, China). Acupoint localization will follow GB/T12346-2021 national standards (Table 3; Figure 2): bilateral HT7: 0.3–0.5 cun (
≈
6–10 mm) perpendicular insertion, avoiding ulnar vasculature; bilateral KI7: 0.5–1.0 cun (
≈
10-20 mm) perpendicular insertion. After piercing, thrusting and twirling of the needle will be performed to induce the sensation of ‘De qi’, and the needle will be left for 20 min (32). De qi means that after the needle has penetrated into the acupoint to a certain depth, the needle is thrusted and twirled to cause the acupoint to obtain the induction of meridian qi. The subjects will have a self-conscious reaction, such as soreness, heaviness or distention. This is the key process in acupuncture treatment (33, 34).

**Table 3 tab3:** Locations of acupuncture points.

Acupoint	Location
HT7	At the ulnar end of the transverse crease of the wrist, in the depression on the radial side of the tendon of muscle flexor carpi ulnaris
KI7	2.0 cun ( ≈40mm ) above the medial malleolus (inner ankle bone), anterior to the Achilles tendon, in the depression between the tibia (shinbone) and the Achilles tendon
Sham HT7	Located about 2.0 cun away from the HT7 along the direction of the ulnar flexor carpi tendon, avoiding the ulnar flexor carpi tendon, at the junction of the red and white flesh between the Heart Meridian and Small Intestine Meridian.
Sham KI7	Located 2.0 cun lateral to the inner belly of the gastrocnemius muscle from KI7, avoiding the course of the Kidney Meridian.

